## Analysis plan

---

Any cancer  
  No asthma  
    Unexposed  
    Exposed  
  Asthma  
    Unexposed  
    Exposed  
Lung cancer  
  No asthma  
    Unexposed  
    Exposed  
  Asthma  
    Unexposed  
    Exposed  
Breast cancer  
  No asthma  
    Unexposed  
    Exposed  
  Asthma  
    Unexposed  
    Exposed  
Prostate cancer  
  No asthma  
    Unexposed  
    Exposed  
  Asthma  
    Unexposed  
    Exposed  
Pancreatic cancer  
  No asthma  
    Unexposed  
    Exposed  
  Asthma  
    Unexposed  
    Exposed  
Melanoma  
  No asthma  
    Unexposed  
    Exposed  
  Asthma  
    Unexposed  
    Exposed  
Keratinocyte cancer  
  No asthma  
    Unexposed  
    Exposed  
  Asthma  
    Unexposed

---

## Analysis plan

---

|                                                                                     |
|-------------------------------------------------------------------------------------|
| Exposed                                                                             |
| Lymphoma                                                                            |
| No asthma                                                                           |
| Unexposed                                                                           |
| Exposed                                                                             |
| Asthma                                                                              |
| Unexposed                                                                           |
| Exposed                                                                             |
| Multiple myeloma                                                                    |
| No asthma                                                                           |
| Unexposed                                                                           |
| Exposed                                                                             |
| Asthma                                                                              |
| Unexposed                                                                           |
| Exposed                                                                             |
| Leukaemia                                                                           |
| No asthma                                                                           |
| Unexposed                                                                           |
| Exposed                                                                             |
| Asthma                                                                              |
| Unexposed                                                                           |
| Exposed                                                                             |
| Meningioma                                                                          |
| No asthma                                                                           |
| Unexposed                                                                           |
| Exposed                                                                             |
| Asthma                                                                              |
| Unexposed                                                                           |
| Exposed                                                                             |
| Cancer of the brain, hypophysis,
corpus pineale and ductus
craniopharyngealis |
| No asthma                                                                           |
| Unexposed                                                                           |
| Exposed                                                                             |
| Asthma                                                                              |
| Unexposed                                                                           |
| Exposed                                                                             |
| Spinal cord, cranial nerve or other
CNS tumours                                  |
| No asthma                                                                           |
| Unexposed                                                                           |
| Exposed                                                                             |
| Asthma                                                                              |
| Unexposed                                                                           |
| Exposed                                                                             |

Estimated hazard ratios from Cox regression with time since index date as underlying timescale, stratified by matched set.

## Analysis plan

Unadjusted: No adjustment.

Mediation model: Adjusted additionally for time-varying lifestyle-related diseases.

### Sensitivity analyses

8. We will examine if the association is reduced by adjustment for time-varying systemic treatment for eczema. The study is likely insufficiently powered to examine for effect measure modification by immunosuppressive treatments.

**Table 8. Number of events, accumulated person-time, and HRs for cancer associated with eczema, Denmark. Adjusting additionally for systemic treatment for eczema.**

|                          | N | events | P-Y
at
risk | Rate
per
1,000 | Hazard ratio and 99%
confidence interval  |                    |
|--------------------------|---|--------|-------------------|----------------------|----------------------------------------------------------|--------------------|
|                          |   |        |                   |                      | Unadjusted                                               | Mediation
model |
| Any cancer               |   |        |                   |                      |                                                          |                    |
| Unexposed                |   |        |                   |                      |                                                          |                    |
| Exposed                  |   |        |                   |                      |                                                          |                    |
| Lung cancer              |   |        |                   |                      |                                                          |                    |
| Unexposed                |   |        |                   |                      |                                                          |                    |
| Exposed                  |   |        |                   |                      |                                                          |                    |
| Breast cancer            |   |        |                   |                      |                                                          |                    |
| Unexposed                |   |        |                   |                      |                                                          |                    |
| Exposed                  |   |        |                   |                      |                                                          |                    |
| Prostate cancer          |   |        |                   |                      |                                                          |                    |
| Unexposed                |   |        |                   |                      |                                                          |                    |
| Exposed                  |   |        |                   |                      |                                                          |                    |
| Melanoma skin cancer     |   |        |                   |                      |                                                          |                    |
| Unexposed                |   |        |                   |                      |                                                          |                    |
| Exposed                  |   |        |                   |                      |                                                          |                    |
| Keratinocyte skin cancer |   |        |                   |                      |                                                          |                    |
| Unexposed                |   |        |                   |                      |                                                          |                    |
| Exposed                  |   |        |                   |                      |                                                          |                    |
| Lymphoma                 |   |        |                   |                      |                                                          |                    |
| Unexposed                |   |        |                   |                      |                                                          |                    |
| Exposed                  |   |        |                   |                      |                                                          |                    |
| Multiple myeloma         |   |        |                   |                      |                                                          |                    |
| Unexposed                |   |        |                   |                      |                                                          |                    |
| Exposed                  |   |        |                   |                      |                                                          |                    |
| Leukemia                 |   |        |                   |                      |                                                          |                    |
| Unexposed                |   |        |                   |                      |                                                          |                    |
| Exposed                  |   |        |                   |                      |                                                          |                    |
| Meningioma               |   |        |                   |                      |                                                          |                    |
| Unexposed                |   |        |                   |                      |                                                          |                    |
| Exposed                  |   |        |                   |                      |                                                          |                    |

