### *Unexposed cohort*

- Up to 10 persons matched to each eczema patient by sex and birth year.
- Comparators have to: (1) be born in Denmark, (2) be alive and living in Denmark on the on index date of their matched eczema-exposed individual (i.e. first hospital eczema diagnosis), and (3) have no previous diagnosis of eczema.
- Index date = The same index date as their matched eczema-exposed individual

As with eczema patients, we will additionally apply the following restrictions:

- We will exclude matched comparators with inconsistencies in registration of status and residence in the Civil Registration System (recorded as alive but not living in Denmark but without an emigration date), as we assume that these patients are not living in Denmark and thus not eligible.
- We will exclude comparators with any cancer (except non-melanoma skin cancer) before or on index date (see Table 2). That is, we will not only exclude those with history of the cancer outcome of interest. However, in analyses of non-melanoma skin cancer specifically, we will exclude those with previous history of this cancer as well.

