### Covariables

We will include various variables, shown in table 3. With the exception of socioeconomic variables, variables are time-updated. Thus, people will contribute person-time in the unexposed category for a given variable until they fulfill the definition for the condition/treatment, after which they will contribute in the exposed category for the remaining follow-up.

**Table 3.** Covariables

| ICD-8 | ICD-10 | Other codes in patient registry | ATC | Notes |
|-------|--------|---------------------------------|-----|-------|
|-------|--------|---------------------------------|-----|-------|

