|                                                                                                    |                  | "DC94" "DC95"
"DC81" "DC82"
"DC83" "DC84"
"DC85" "DC86"
"DC88" "DC96"           |                                        |
| Use of oral corticosteroids                                                                        |                  | "H02AB" and
DOSFOR M "TAB"
or
"TABMO D"                                            | Any prescription excluding injections. |
| Systemic treatment for eczema (cyclosporine, azathioprine, mycophenolate, methotrexate, dupilumab) | Procedure codes: | "L04AX0 1"
"BOHJ18 B8"
"BWHB83 3"
"BWAH1 15"
"BOHJ20"
"BOHJ22"
"D11AH0 5" |                                        |
| Asthma                                                                                             | "493"            | "DJ45" "DJ46"                                                                               |                                        |

Note: All subcodes are included unless otherwise stated; all types of contacts (inpatient, outpatient and emergency) and both primary and secondary diagnoses should be considered. Use admission/prescription/record date for all variables.

aBaseline information only

bDocumentation is available here:

<https://www.dst.dk/da/Statistik/dokumentation/Times/forskningsservice/efalle>

<https://www.dst.dk/da/Statistik/dokumentation/Times/cpr-oplysninger/c-faelle-id>

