 Unexposed  
 Exposed  
 Leukemia  
 Unexposed  
 Exposed  
 Meningioma  
 Unexposed  
 Exposed  
 Cancer of the brain, hypophysis,  
 corpus pineale and ductus  
 craniopharyngealis  
 Unexposed  
 Exposed  
 Spinal cord, cranial nerve and  
 other CNS tumours  
 Unexposed  
 Exposed

---

Estimated hazard ratios from Cox regression with time since index date as underlying timescale, stratified by matched set.

Unadjusted: No adjustment.

Mediation model: Adjusted additionally for time-varying lifestyle-related diseases.

10. We will repeat the main analysis additionally adjusting for immunosuppression (immunosuppressive disorders or drugs).

---

**Table 10. Number of events, accumulated person-time, and HRs for cancer associated with eczema, Denmark. Adjusting additionally for immunosuppression.**

---

|                 | N | events | P-Y
at
risk | Rate
per
1,000 | Hazard ratio and 99%
confidence interval  |                    |
|-----------------|---|--------|-------------------|----------------------|----------------------------------------------------------|--------------------|
|                 |   |        |                   |                      | ‘Unadjusted’                                             | Mediation
model |
| Any cancer      |   |        |                   |                      |                                                          |                    |
| Unexposed       |   |        |                   |                      |                                                          |                    |
| Exposed         |   |        |                   |                      |                                                          |                    |
| Lung cancer     |   |        |                   |                      |                                                          |                    |
| Unexposed       |   |        |                   |                      |                                                          |                    |
| Exposed         |   |        |                   |                      |                                                          |                    |
| Breast cancer   |   |        |                   |                      |                                                          |                    |

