Unadjusted: Adjusted additionally for **immunosuppression**.

Mediation model: Adjusted additionally for time-varying lifestyle-related diseases **and immunosuppression**.

11. We will repeat the main analysis additionally adjusting for use of **oral corticosteroids**. We will define use as a time-updated never/ever variable. Thus, individuals classified as exposed if they ever have a prescription for an oral corticosteroid, with status changing at the first prescription for an oral corticosteroid.

---

**Table 11. Number of events, accumulated person-time, and HRs for cancer associated with eczema, Denmark. Adjusting additionally for oral glucocorticoids.**

---

| N | events | P-Y
at
risk | Rate
per
1,000 | Hazard ratio and 99%
confidence interval  |                    |
|---|--------|-------------------|----------------------|----------------------------------------------------------|--------------------|
|   |        |                   |                      | ‘Unadjusted’                                             | Mediation
model |

---

---

|                                  |
|----------------------------------|
| Any cancer                       |
| Unexposed                        |
| Exposed                          |
| Lung cancer                      |
| Unexposed                        |
| Exposed                          |
| Breast cancer                    |
| Unexposed                        |
| Exposed                          |
| Prostate cancer                  |
| Unexposed                        |
| Exposed                          |
| Melanoma skin cancer             |
| Unexposed                        |
| Exposed                          |
| Keratinocyte skin cancer         |
| Unexposed                        |
| Exposed                          |
| Lymphoma                         |
| Unexposed                        |
| Exposed                          |
| Multiple myeloma                 |
| Unexposed                        |
| Exposed                          |
| Leukemia                         |
| Unexposed                        |
| Exposed                          |
| Meningioma                       |
| Unexposed                        |
| Exposed                          |
| Cancer of the brain, hypophysis, |
| corpus pineale and ductus        |
| craniopharyngealis               |
| Unexposed                        |
| Exposed                          |

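### Item 8 gives systemic treatment one coefficient across both cohorts, so the adjusted eczema HR can fall although treatment has no effect in eczema patients

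*Protocol*

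**What the plan says.** The secondary aim in the protocol's opening section asks whether the risk depends on, among other things, systemic immunosuppressive treatments. Item 8 under Sensitivity analyses is the analysis closest to that part of the aim: "We will examine if the association is reduced by adjustment for time-varying systemic treatment for eczema". It adds that "The study is likely insufficiently powered to examine for effect measure modification by immunosuppressive treatments", so no product term is planned and one treatment coefficient serves both cohorts.

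The covariate is listed in the covariables table as "Systemic treatment for eczema (cyclosporine, azathioprine, mycophenolate, methotrexate, dupilumab" and is identified by procedure and ATC codes, with no indication required. The Covariables section applies it to everyone as a time-updated never/ever state: "people will contribute person-time in the unexposed category for a given variable until they fulfill the definition for the condition/treatment".

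Under Unexposed cohort, comparators must "have no previous diagnosis of eczema", with up to 10 per patient. Under Follow-up they are censored if eczema is diagnosed. The model is a Cox regression stratified on matched set.

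**The concern.** In the eczema cohort the covariate marks, for the most part, treatment of eczema. In the comparison cohort it marks mostly treatment of something else. This is inferred from the cohort definitions. The protocol does not say it, and comparators with eczema never recorded in hospital are not ruled out.

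A diagnosis that leads to these drugs may carry its own cancer risk. A single coefficient then averages the comparators' disease-related risk with whatever treatment does in eczema patients, and applies the average to both. If eczema patients are treated more often, part of their association with cancer is moved into the treatment term. The resulting fall is the signal that item 8 sets out to look for, so Table 8 could suggest that treatment accounts for an association when it accounts for none of it.

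**Working it through.** The protocol states no expected HR, event count or frequency of treatment, so there is no figure to reproduce. The inputs below are assumptions, except the 10:1 ratio, which is the protocol's maximum.

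**Inputs**
- p1, p0: share of person-time after first systemic treatment in eczema patients and in comparators.
- H: true HR of untreated eczema against untreated comparators.
- R1: HR of treated against untreated eczema patients. R1 = 1 means that treatment has no effect and marks no extra risk.
- R0: the same ratio in comparators.

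**Formulas** (large-sample Poisson form, comparator baseline rate 1, 10 comparator person-years per eczema person-year)
- Comparator events D0 = 10 × (1 − p0 + p0·R0)
- Eczema events D1 = H × (1 − p1 + p1·R1)
- Treated events Dt = 10·p0·R0 + H·p1·R1
- Unadjusted HR = D1 / (D0/10)
- The shared drug coefficient θ solves D0·p0·θ/(1 − p0 + p0·θ) + D1·p1·θ/(1 − p1 + p1·θ) = Dt
- Adjusted HR = unadjusted HR × (1 − p0 + p0·θ)/(1 − p1 + p1·θ)

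The last line gives the conditions. With θ > 1 the factor is below 1 only if p1 > p0, and when R1 = 1, θ exceeds 1 only if R0 > 1.

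**Worked case:** p1 = 10%, p0 = 1%, H = 1.10, R1 = 1, R0 = 2.
- D0 = 10 × 1.01 = 10.1; D1 = 1.10; Dt = 0.20 + 0.11 = 0.31
- Unadjusted HR = 1.10/1.01 = 1.089
- θ = 1.511, although the true ratio in eczema patients is 1
- Adjusted HR = 1.089 × 1.00511/1.05112 = 1.041

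**Other cases, R1 = 1.** The matched-set column maximises the expected stratified partial likelihood for risk sets of one patient and 10 comparators.

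| Use, eczema vs comparators | R0 | True HR | Unadjusted | Shared term, Poisson | Shared term, matched set |
|---|---|---|---|---|---|
| 3% vs 0.5% | 1.3 | 1.10 | 1.098 | 1.093 | 1.093 |
| 5% vs 1% | 2 | 1.10 | 1.089 | 1.061 | 1.063 |
| 10% vs 1% | 2 | 1.10 | 1.089 | 1.041 | 1.044 |
| 10% vs 1% | 3 | 1.10 | 1.078 | 0.987 | 0.995 |
| 15% vs 2% | 3 | 1.10 | 1.058 | 0.914 | 0.929 |
| 10% vs 1% | 1 | 1.10 | 1.100 | 1.100 | 1.100 |
| 10% vs 1% | 0.8 | 1.10 | 1.102 | 1.112 | 1.112 |
| 10% vs 10% | 2 | 1.20 | 1.091 | 1.091 | 1.098 |
| 5% vs 10% | 2 | 1.20 | 1.091 | 1.140 | 1.144 |

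Up to 10% vs 1% use and R0 = 3, the fall is 0.005 to 0.092 (Poisson) or 0.005 to 0.083 (matched set). The 15% vs 2% row with R0 = 3 gives 0.13 to 0.14. With R0 of 1 or below, or with use not commoner in eczema, the HR does not fall.

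A cohort-specific treatment term returns the true HR in untreated person-time in every one of these cases.

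**What that untreated HR cannot do.** Let treatment be inert but treated eczema be more severe, with R1 = 2 from severity alone, p1 = 10%, p0 = 1%, H = 1.10 and R0 = 1. The unadjusted HR is 1.10 × 1.10 = 1.21. The shared term gives 1.16. The before-treatment HR is 1.10 and the after-treatment HR is 1.10 × 2 = 2.20. The untreated HR is therefore also below the unadjusted one, with no treatment effect at all.

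**The case against.** The strongest defence has four parts.

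- **The condition is unproven.** The protocol gives neither the frequency of treatment nor the cancer risk of treated comparators, so a reader who infers that the adjusted HR must fall goes too far. This stands: the fall is conditional and can be negligible.
- **A similar contrast is already planned.** The severity analysis (item 6) reports moderate eczema, which is person-time before any severity criterion is met, against comparators. A misleading Table 8 could be noticed beside it. This stands in part. That analysis is restricted to index dates from 1996, its severe group also takes in phototherapy and admission for eczema, and its reference is all comparators.
- **Power.** Item 8 sets effect modification aside for lack of power. That is a reason not to test an interaction. Leaving the term out does not avoid the question, because it assumes that the two coefficients are equal. Estimating the eczema HR before treatment needs no interaction test.
- **No stated inference.** The protocol nowhere says that a reduction will be taken as proof that treatment explains the association. True, but a reduction is the one result that item 8 says it will examine.

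Three further inferences are tempting but unsupported. First, a reader might extend the point to items 10 and 11, which share the model form. Those items only repeat the main analysis with added adjustment and state no such reading. Item 10 also covers immunosuppressive disorders, for which a common coefficient is ordinary confounder adjustment. Second, a reader might take the untreated HR as the right adjusted answer. The severity example shows that it is not, and systemic treatment is itself one of the protocol's criteria for severe eczema. Third, a reader might suppose that comparators dominate the shared coefficient. At 10% vs 1% use, treated person-time is equal (10 × 0.01 against 1 × 0.10).

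**Conclusion.** The point holds for item 8, as a conditional one. The shared coefficient can produce a false reduction if treated comparators have a raised cancer risk and treatment is commoner among eczema patients. Both are plausible, but the protocol quantifies neither. Under the assumed inputs the false fall is about 0.005 to about 0.09 on a true HR of 1.10, and larger only at the most extreme combination tried. At the upper end it removes the whole apparent excess. As specified, Table 8 cannot tell this artefact from a real contribution of treatment. The primary analysis is unaffected, and items 10 and 11 are not part of the claim.

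**What to change.** In item 8, keep the planned model and add a second one with a cohort-specific treatment term. Report in Table 8 separate HRs for eczema person-time before and after first systemic treatment, each against untreated comparators. In the worked case both would be 1.10 beside a shared-term HR of 1.041, which exposes the false fall.

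Add two sentences to the item:
- A fall under the shared coefficient alone will not be read as treatment explaining the association.
- The before-treatment HR applies to untreated, probably milder, eczema, and so cannot by itself separate treatment from severity.

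The cost is one extra model from data already held, two more rows per outcome, and slightly fewer events in the untreated contrast. The structure is that of the time-updated severity analysis, and no interaction test is needed.
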